All households selected for the DIUPG Bangladesh programme contain a person with a disability. The unit of participation in the programme is the household; however, a single individual within each household is the ‘project participant’ who is the primary recipient of the assets and rehabilitation and psychosocial support delivered by the DIUPG Bangladesh programme. All project participants in DIUPG are persons with disabilities (i.e. the pre-identified index individual within each enrolled household who is the target beneficiary of the intervention components). In the majority of cases, project participants take direct responsibility for management of the provided asset and participate in programme activities, such as enterprise development training or savings group meetings. However, where they are individuals with severe disabilities or children, management of the asset and participation in some project activities (e.g. Village Social Solidarity Committee meetings) is undertaken by their caregiver or another family member. If a household contains multiple individuals with disabilities, only one is registered as the primary participant. Other persons with disabilities in the household may receive support (e.g. rehabilitation and psychosocial training) where relevant, but they are not formal programme participants and do not receive livelihood assets.

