### Outcomes {12}

As poverty is multidimensional, this evaluation therefore specifies five primary outcomes across key economic dimensions aligned with the DIUPG Theory of Change. The five primary outcomes focus on (1) per capita household income, (2) income of persons with disabilities, (3) employment of persons with disabilities, (4) per capita food consumption and expenditures, and (5) per capita non-food expenditures. Secondary outcomes include financial inclusion, assessed through savings and credit access for persons with disabilities and other household members; psychological and mental well-being; health-seeking behaviour; and social inclusion of persons with disabilities. Individual-level outcomes are collected for the household’s index participant with disability only (i.e. the designated DIUPG participant or their equivalent).

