Programme impacts will be estimated under the intention-to-treat (ITT) principle using the following cross-sectional regression model for continuous outcomes:2$${y}_{ibd}=\alpha +\upbeta {T}_{bd}+{\tau}_{d}+{\varepsilon}_{ibd}$$where $${y}_{ibd}$$ is post-intervention outcome variable (including pre-specified primary and secondary outcomes such as per capita household income, income of persons with disabilities, per capita food consumption and expenditures, and per capita non-food expenditures, etc.); $${T}_{bd}$$ is an indicator variable taking the value of 1 if individual or household i is assigned to the treatment group and 0 if assigned to the control group; $${\tau}_{d}$$ are district fixed effects and $${\varepsilon}_{ibd}$$ are error terms. We will cluster standard error by branch office catchment area level, the unit of randomisation. The key parameter of interest is $$\upbeta$$ which measures the effect of the programme on the outcome variable.

Employment status is a binary outcome and will be analysed using logistic regression, with treatment assignment included as the primary explanatory variable and district fixed effects to account for stratified randomisation. Standard errors will be clustered at the branch office (catchment) level, the unit of randomisation, using cluster-robust estimators. Results will be reported as odds ratios with corresponding confidence intervals and *p*-values.

The primary model specification is fixed and will not be modified based on statistical significance or model fit.

Given five specified primary outcomes, we will control the family-wise type I error rate at two-sided *α* = 0.05 across the primary outcome family using a Bonferroni correction. Accordingly, each primary outcome hypothesis test will be conducted at a two-sided significance level of *α* = 0.01 (0.05/5). We will report effect estimates and confidence intervals for each primary outcome alongside *p*-values; where confidence intervals are used for inference, Bonferroni-adjusted 99% confidence intervals will be reported alongside effect estimates and *p*-values.

Secondary outcomes will be analysed as exploratory. For these outcomes, we report effect estimates, 95% confidence intervals, and nominal two-sided p-values without formal multiplicity adjustment. Secondary findings will not be used to determine overall intervention effectiveness.

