Inference is conducted separately for each outcome within the multiplicity-adjusted framework, and interpretation will emphasise effect magnitude and precision rather than binary declarations of overall “success”.

We will additionally report covariate-adjusted models as supplementary analyses. The equation for models with continuous outcomes is:$${y}_{ibd}=\alpha +\beta {T}_{bd}+\gamma {X}_{ibd}+{\tau}_{d}+{\varepsilon}_{ibd}.$$

Here, $${X}_{ibd}$$ is the baseline value of the post-intervention outcome variable, $${y}_{ibd}$$. No additional covariates will be selected. This approach improves statistical precision while preserving the unbiasedness of the treatment effect under random assignment. The same approach will be used for the binary outcome of employment. These adjusted models are interpreted as sensitivity analyses.

Continuous outcomes will be analysed on their natural scale in the primary specification. Where outcomes are substantially right-skewed (e.g. income or expenditure variables), log-transformed models will additionally be reported as robustness analyses. These alternative specifications will be applied consistently across relevant outcomes and reported transparently.

Because assignment may not perfectly determine treatment receipt, the primary model estimates the intention-to-treat (ITT) effect. In the presence of non-compliance, this differs from the effect of actual treatment receipt. As an exploratory analysis, we estimate the local average treatment effect (LATE) using two-stage least squares, with assignment serving as an instrument for treatment receipt.

Due to the 2:1 cluster allocation ratio between the intervention and control arms and variables corresponding to programme exposure, it is not feasible to conduct a blinded analysis of trial data, which represents a limitation of the study.

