### Methods in analysis to handle protocol non-adherence and any statistical methods to handle missing data {20c}

The full analysis set (FAS) will be specified according to the intention-to-treat (ITT) principle and will include all randomised participants analysed according to the study arm to which they were assigned at randomisation, irrespective of programme uptake or protocol deviations.. The primary analysis will estimate treatment effects using regression models applied to all available outcome data. Participants with missing outcome data will therefore not contribute to the estimation of treatment effects. This approach assumes that outcomes are missing at random (MAR) conditional on district. We will report the extent of missingness by study arm for each outcome and compare baseline characteristics between participants with observed and missing outcomes to assess potential differential attrition. Where possible, reasons for withdrawal for each group will be reported descriptively by study arm.

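### The planned log-transformed robustness model is a poor choice for income of persons with disabilities, where zero incomes are to be expected

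*Protocol article*

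**What the plan says.** Under Statistical methods for primary and secondary outcomes {20a}, the primary rule is "Continuous outcomes will be analysed on their natural scale in the primary specification". The next sentence adds that "Where outcomes are substantially right-skewed (e.g. income or expenditure variables), log-transformed models will additionally be reported as robustness analyses", and the one after it says "These alternative specifications will be applied consistently across relevant outcomes and reported transparently". Income is named as an example. No exception is made for outcomes that can be zero.

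Outcomes {12} lists among the five primary outcomes "2) income of persons with disabilities, (3) employment of persons with disabilities". It also says that individual-level outcomes come from the household's "index participant with disability only (i.e. the designated DIUPG participant or their equivalent".

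Eligibility criteria {10} requires a person with a disability aged 1 to 62. It explains that, "where they are individuals with severe disabilities or children, management of the asset" and some project activities pass to a caregiver or relative.

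On the neighbouring outcome, section {20a} states: "Employment status is a binary outcome and will be analysed using logistic regression". The full analysis set in section {20c} "will include all randomised participants analysed according to the study arm to which they were assigned at randomisation".

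**The concern.** The logarithm of zero is undefined. An outcome measured on index persons who include small children and people with severe disabilities will very probably contain zeros. The planned log model then has two ordinary completions, and neither is a sound check on the primary estimate.

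- **Drop the zeros.** The model compares people with positive income in one arm with people with positive income in the other. Having an income is decided after randomisation and is something the programme sets out to change. The two groups are no longer comparable by design, and people with a valid outcome of zero leave an analysis meant to include everyone randomised.
- **Add a constant.** Everyone stays in, but the coefficient depends on the constant and on whether income is in taka or thousands of taka. It cannot be read as a percentage effect.

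At stake is how a primary result is read. A log model reported as a robustness check could seem to contradict a sound natural-scale estimate, or show nothing where there is a gain. The Trial status section says endline data were collected in October–November 2025, and section {20a} says blinded analysis is not feasible. A choice left until analysis would therefore be made with allocation known.

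**Working it through.** The article gives no share of zero incomes and no earnings distribution, so there is no figure of its own on this point to reproduce. The inputs below are assumptions, and a range is shown.

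**Set-up.** Let p0 be the share with positive income in control, dp the added share with positive income under the programme, g the log gain among those who would earn anyway, and r the income of new earners relative to the usual level. With the same spread of log income in each group:

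- ratio of arm means, zeros kept: (p0·e^g + dp·r)/p0 = e^g + dp·r/p0
- log difference among positive incomes only: (p0·g + dp·ln r)/(p0 + dp)

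The second is negative when dp·(−ln r) > p0·g.

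**Worked case.** p0 = 0.30, dp = 0.10, g = 0, r = 0.5.

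- Mean ratio: 1 + 0.10 × 0.5/0.30 = 1.17.
- Log difference: 0.10 × ln 0.5/0.40 = −0.0693/0.40 = −0.173, which is about −16%.

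With g = 0.10 the mean ratio is 1.105 + 0.167 = 1.27. The log difference is (0.030 − 0.0693)/0.40 = −0.098, about −9%.

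**Range.**

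| p0 | dp | g | r | Mean ratio | Log difference, positive incomes |
|---|---|---|---|---|---|
| 0.30 | 0.05 | 0 | 0.5 | 1.08 | −0.099 |
| 0.30 | 0.10 | 0 | 0.5 | 1.17 | −0.173 |
| 0.30 | 0.10 | 0.10 | 0.5 | 1.27 | −0.098 |
| 0.30 | 0.20 | 0.10 | 0.5 | 1.44 | −0.217 |
| 0.60 | 0.10 | 0 | 0.5 | 1.08 | −0.099 |
| 0.60 | 0.10 | 0.10 | 0.7 | 1.22 | +0.035 |
| 0.30 | 0.10 | 0 | 1 | 1.33 | 0 |
| 0.30 | 0.10 | 0.10 | 1 | 1.44 | +0.075 |
| 0.30 | 0 | 0.10 | any | 1.11 | +0.100 |

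The sign turns only when the programme adds earners (dp > 0) who earn less than the others (r < 1) by enough to meet the condition above. At r = 1 the benefit is missed or understated but not reversed. At dp = 0 the log model is sound.

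**In a trial of this size.** One thousand trials were simulated per case with the article's 48 and 24 clusters of 35 and ICC 0.055 (placed on log income), with cluster-robust standard errors and no district effects. Log SD 0.8 and median income 3000 BDT are assumed. Significance is at the two-sided 5% level.

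- p0 = 0.30, dp = 0.10, g = 0, r = 0.5: the log coefficient was negative in 99% of trials and significantly negative in 63%, using 37% of participants. The natural-scale estimate was significantly positive in 38%.
- p0 = 0.30, dp = 0.20, g = 0.10, r = 0.5: significantly negative on logs in 83%, significantly positive on the natural scale in 96%.
- p0 = 0.30, dp = 0.10, g = 0.20, r = 0.7: mean log coefficient +0.06, negative in 20%.

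**Adding a constant.** In the worked case log(y + 1) gives about +0.73 with income in BDT (0.10 × ln 1500 = 0.73) and about +0.10 with income in thousands of BDT. The data are the same and the answers differ sevenfold.

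**The case against.** The strongest reply is that no primary conclusion depends on this. The primary model is on the natural scale, keeps zeros, and is stated to be fixed regardless of significance or fit. The log models are additional. That stands, and it limits the weight of the point.

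A second reply is that the article does not say zeros will be dropped, and the handling of zeros in a robustness model is the kind of detail an analysis plan supplies. The first part stands: a reader might infer that the plan conditions on being employed, but the text does not say so. The second part does not dispose of the point, because both usual ways of completing the rule give a poor answer for this outcome. The weakness lies in naming income for a log model.

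Third, a reader might infer that everyone out of work has zero income. The documents do not support this. They define neither income nor employment for these persons, the programme helps participants obtain government entitlements that might count as income, and the attribution of income from a caregiver-managed asset is not stated. Positive income and employment are closely related but need not coincide, and the share of zeros is unknown.

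Fourth, the log model is not the only sensitivity analysis. Models adjusted for the baseline value are also planned, though they do not address skew. The point should also not be stretched to household income through loss-making enterprises, which the documents do not mention, or to food and non-food expenditure, where zeros should be rare.

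Finally, a log-link model still targets means, so it partly re-expresses the primary contrast and does not tame extreme incomes. That is true, and it is a cost of the remedy.

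**Conclusion.** The point holds for one primary outcome, income of persons with disabilities, and for a robustness analysis only. There the planned log model would either select on a post-randomisation state or depend on an arbitrary constant and unit. It could miss a real gain (log difference 0 against a mean ratio of 1.33) or show the opposite sign (−0.17 against 1.17).

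A reader might infer that reversal is the expected result. It is not: it requires the programme to bring in new earners who earn sufficiently less than existing ones. That is plausible for newly started enterprises, but the documents do not establish it. All magnitudes rest on assumed shares and earnings. The expectation that there will be some zeros rests on the document's own account of who the index persons are.

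**What to change.** For income of persons with disabilities, and any other outcome with a material share of zeros, replace the log-transformed robustness model with a log-link model on the raw outcome, fitted by Poisson pseudo-maximum-likelihood with district effects and the same branch-level cluster-robust inference. This keeps every participant with outcome data, zeros included, and estimates the ratio of arm means. Keep log-transformed models for outcomes whose values are all positive. Record the change before endline income is analysed.

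The cost is about one sentence in the plan and one command per affected outcome, with no new data. The downside is small: the log-link model remains sensitive to extreme incomes, and the report should say so.

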### Interim analyses {21b}

No interim analyses planned.

### Methods for additional analyses (e.g. subgroup analyses) {20b}

In addition to estimating the average treatment effect, we will also explore heterogeneity in the treatment effects across different subgroups. Specifically, we will test for variations in the programme’s impact based on disability severity and female-headed households and estimate:$${y}_{ibd}=\alpha +\beta {T}_{bd}+\delta Zibd+\theta (Tbd\times Zibd)+{\tau}_{d}+{\varepsilon}_{ibd}.$$where $${Z}_{ibd}$$ is either baseline disability severity or an indicator for female-headed households. The coefficient $$\theta$$ tests for differential programme impacts across categories defined by $${Z}_{ibd}$$. Standard errors will be clustered at the branch office catchment area level (unit of randomisation), and district fixed effects ($${\tau}_{d}$$) will be included. Disability severity is defined using scores from the WG SS at baseline. This is a multi-category variable, we will use indicator variables for severity categories (with the lowest severity category as reference). Female-headed households will be defined as households in which the primary decision-maker/household head is female at baseline. These interaction analyses are exploratory.

### Methods in analysis to handle protocol non-adherence and any statistical methods to handle missing data {20c}

The full analysis set (FAS) will be specified according to the intention-to-treat (ITT) principle and will include all randomised participants analysed according to the study arm to which they were assigned at randomisation, irrespective of programme uptake or protocol deviations.. The primary analysis will estimate treatment effects using regression models applied to all available outcome data. Participants with missing outcome data will therefore not contribute to the estimation of treatment effects. This approach assumes that outcomes are missing at random (MAR) conditional on district. We will report the extent of missingness by study arm for each outcome and compare baseline characteristics between participants with observed and missing outcomes to assess potential differential attrition. Where possible, reasons for withdrawal for each group will be reported descriptively by study arm.

### Plans to give access to the full protocol, participant-level data and statistical code {31c}

Twelve months after the end of the study, the anonymised survey data will be made available on LSHTM’s Data Compass (datacompass.lshtm.ac.uk), for which explicit consent has been included in the consent form, alongside project documentation and a data user guide.

## Oversight and monitoring

### Composition of the coordinating centre and trial steering committee {5d}

BRAC is responsible for the intervention design, allocation, implementation, and programme monitoring. BIGD leads data collection for the evaluation, with support from LSHTM. Evaluation design and analysis is led by LSHTM, in partnership with BIGD. Monitoring data collected from BRAC is shared with LSHTM and BIGD for the purpose of the process evaluation.

### Composition of the data monitoring committee, its role and reporting structure {21a}

As the evaluation is not blinded and the interventions pose a limited risk to participants, a data monitoring committee is not required.

### Adverse event reporting and harms {22}

Delivery of the DIUPG Bangladesh programme is monitored by BRAC. The intervention by design is targeted at households who have a member with disability and who meet the criteria for being ultra-poor. This means that many households in villages where the programme is delivered will not receive it as they are ineligible. It is possible that this will generate resentment within the villages. Resentment may lead to perpetration of stigma and discrimination, violence or theft, particularly targeting persons with disabilities. Indeed, infrequent instances of this were observed within the DIUPG Uganda programme [9]. Such events are monitored by BRAC through a feedback and complaint-handling mechanism and will also inform the DIUPG Bangladesh process evaluation.

### Frequency and plans for auditing trial conduct {23}

Data is quality assured in the field by the data collection team supervisor through regular oversight according to protocols, including daily reviews of submitted forms, spot checks during interviews, and direct feedback to data collectors. It is also checked after submission by the data manager. Any discrepancies are followed up with the relevant data collector as required.

### Plans for communicating important protocol amendments to relevant parties (e.g. trial participants, ethical committees) {25}

Any important modifications to the study protocol are agreed between BRAC, BIGD and LSHTM, and approved by LSHTM Ethics Committee and James P Grant School of Public Health Ethics Committee prior to implementation.

### Dissemination plans {31a}

To disseminate findings from this research, we will write academic articles and evidence briefings, present at conferences and publicise the results through other communications within a network of academic and non-academic partners. There will also be community dissemination activities.

## Discussion

The ultra-poor graduation model has been shown to be effective for the mainstream population of the ultra-poor across several different contexts [1] and the UPG approach has been adapted to be disability-inclusive. An evaluation of the DIUPG programme in Uganda showed that the programme successfully increased household consumption expenditures, despite operating amidst challenging conditions such as COVID-19 and funding cuts [9]. There is a general paucity of evidence regarding what interventions work to create better livelihoods for persons with disabilities and their families [6]. Evaluating the DIUPG Bangladesh programme will generate crucial evidence demonstrating whether similar benefits of the disability-inclusive ultra-poor graduation programme in Uganda are observed in the distinct context of Bangladesh. Aside from the empirical gap this addresses, this information is a boon for policymakers looking for successful livelihood approaches that can be adapted and scaled in their setting.

## Trial status

This manuscript is based on protocol version 2, 05/03/2026. Baseline data collection and recruitment were conducted in May–June 2023. The manuscript was updated on 12/09/2025 to reflect that the endline evaluation is planned for September–October 2025, instead of July–August 2025. The manuscript was updated on 05/03/2026 to respond to first-round peer review comments and to clarify that the endline evaluation took place in October–November 2025.

## Data Availability

Survey data will be made available on LSHTM’s Data Compass 12 months after the end of the study, along with project documentation and a data-users guide. The data will be made available open access, ensuring that no identifiers are included in the data. Explicit consent has been included for making data open access.

## Abbreviations

BIGD: BRAC Institute of Governance and Development
DIUPG: Disability-inclusive ultra-poor graduation programme
FAS: Full analysis set
ICC: Intraclass correlation coefficient
ITT: Intention-to-treat
LSHTM: London School of Hygiene & Tropical Medicine
MDE: Minimum detectable effect
PENDA: Programme for Evidence to Inform Disability Action
RCT: Randomised controlled trial
SD: Standard deviation
SDG: Sustainable Development Goals
SSNP: Social Safety Net Programmes
ToC: Theory of change
UK: United Kingdom
UPG: Ultra-Poor Graduation programme
VSSC: Village Social Solidarity Committee
WGSS: Washington Group Short Set
